### Participant timeline

2.7

The total study duration will be 16 weeks, including a 12-week treatment period and a 4-week follow-up period. A flow chart depicting the study design is presented in Figure 2.

**Figure 2 F2:**
[figure not shown]
The study design flowchart showing details of the randomized controlled trial.

### Safety assessment and adverse events

2.8

Safety assessment for all subjects will be performed via clinical laboratory examination at baseline, before drug administration; 4 weeks after drug administration (visit 2); and 12 weeks, after completing drug administrations (visit 4). Laboratory tests will include those for live rand renal function, which can possibly be damaged by herbal medicines,^[2]^ and serum potassium concentration because *Glycyrrhiza radix*, a component of YKSCH, can induce hypokalemia.^[3]^ Adverse events will be defined as undesirable and/or unexpected medical findings which did not occur before the start of this clinical trial, and will be recorded, regardless of their relation to YKSCH or the placebo drug. The severity of the adverse events will be evaluated based on the step-wise criteria established by the chief investigator, and reported to the IRB of Daejeon University. Following appropriate deliberation, the IRB will determine whether the trial should be discontinued. Causal link between the adverse events and the procedure will be investigated by the doctor-in-charge, and categorized into 6 stages based on the aforementioned evaluation criteria. In case of a severe adverse event, appropriate treatment and follow-up will be provided.

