**Discussion and conclusions::**

This trial will evaluate the effectiveness and safety of YKSCH for sleep improvement in PD with sleep disturbance, and investigate the underlying mechanism of action. We expect improvement in the scores for subjective and objective sleep scales, hemodynamic changes in prefrontal cortical activity, and changes in neurotransmitter and hormone levels. The findings will provide insight into the mechanism underlying the therapeutic effect of YKSCH in PD, and lay the foundation for further studies on whether YKSCH improves sleep disturbance in PD.

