#### Inclusion criteria

2.3.1

A diagnosis of PD made by a neurologist; SCOPA -night score ≧7; Hoehn and Yahr Scale stage 1–4; and provision of informed consent.

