#### Exclusion criteria

2.3.2

Patients with Alzheimer's dementia, vascular dementia, Huntington's disease, amyotrophic lateral sclerosis, or hydrocephalus; gait disturbance caused by stroke, brain tumor, or other brain diseases; a diagnosis of gastrointestinal disease, endocrine disease, or cardiovascular disease not controlled by diet or medication; clinical laboratory abnormality, such as serum creatinine ≥97 mmol/L, alanine amino transferase ≥ 40 U/L, aspartate amino transferase ≥ 40 U/L; unstable medical condition, as decided by the research clinician; administration of herbal medication for PD within the last 4 weeks; and inability to undergo fNIRS. Furthermore, patients may be considered ineligible to participate in this clinical study for other reasons, according to the coordinator's discretion

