##### Scales for outcomes in PD-sleep scale

2.6.1.1

The score of SCOPA-S, which is a questionnaire survey assessing problems in both night- and day-time sleep, and the measurement of PD^[4,9,21]^ the severity will be the primary outcomes measured in this study. The survey will be conducted at baseline (visit 1) and 12 weeks after treatment (visit 4) for both groups.

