#### Instruments to assess sleep disturbance in PD

2.6.3

Parkinson's Disease Sleep Scale (PDSS), Epworth Sleep Scale (ESS), NPI, Beck Depression Inventory (BDI), and Perceived Stress Scale (PSS) scores will be assessed at visits 1–5 for both groups. The PDSS and ESS are valid tools for evaluating sleep disturbance in PD^[22]^ and measuring day-time sleepiness,^[23]^ respectively. For assessing several symptoms related to sleep disturbance, NPI,^[24]^ BDI,^[6]^ and PSS^[25]^ scores will be assessed as secondary outcomes. The NPI is considered a valid instrument to evaluate behavioral and psychological symptoms, including sleep disorder.^[24]^ The BDI will be used to assess depression, one of the leading causes of insomnia.^[6]^ Stress is also known to be associated with sleep quality, and the PSS assesses subjective appraisals of stressful situations.^[25]^

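### The adverse-event definition covers only findings absent before the trial and does not count worsening of a pre-existing condition, so such worsening may escape adverse-event grading, causality review and IRB reporting

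*Protocol article*

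**What the plan says.** Section 2.8 gives the definition: "Adverse events will be defined as undesirable and/or unexpected medical findings which did not occur before the start of this clinical trial". It adds that such findings "will be recorded, regardless of their relation to YKSCH or the placebo drug". Events are then graded for severity, assessed for causality in six categories and reported to the IRB, which decides whether the trial should be discontinued.

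Three other places use adverse events or depend on them:

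- Section 2.5 lists their occurrence among the criteria for discontinuing the allocated intervention.
- Section 2.10 has the independent monitoring committee investigate them.
- The abstract states the aim: "This trial will evaluate the effectiveness and safety of YKSCH for sleep improvement in PD with sleep disturbance".

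On who enters, Section 2.3.1 requires "A diagnosis of PD made by a neurologist; SCOPA -night score ≧7; Hoehn and Yahr Scale stage 1–4". Section 2.3.2 excludes "a diagnosis of gastrointestinal disease, endocrine disease, or cardiovascular disease not controlled by diet or medication", so controlled disease of these kinds may enter.

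**The concern.** The definition turns on newness: a finding qualifies if it did not occur before the trial started. The usual second limb, worsening of something already present, is not there. This matters more here than in a healthy population, because every subject starts with a progressive disease and with the symptom under treatment. Harm in such patients can show itself as more of what they already have.

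An event outside the definition is not graded, not assessed for causality and not sent to the IRB as an adverse event. The safety half of the stated aim would then rest on an incomplete count. If the clause can be read in two ways, the count also depends on who reads it. With 17 subjects per arm, a few events either way would change the safety statement.

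**Working it through.** The plan gives no figure to reproduce, and no sample-size, power or alpha calculation bears on the point. The check sets the sections side by side.

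**1. Applying the definition to four kinds of event**

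- *A condition the subject has never had.* It meets the definition.
- *A new manifestation of an existing disease*, such as a first fall in a patient with PD. It arguably meets the definition, since that particular finding did not occur before.
- *The same symptom at greater severity.* The symptom did occur before, so on the plain reading it does not meet the definition. It qualifies only if the investigator treats the new grade as a separate finding.
- *The same symptom more often.* On the plain reading it does not meet the definition, and the argument for treating it as a separate finding is weaker.

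The clause about relation to the study product ("will be recorded, regardless of their relation to YKSCH or the placebo drug") does not help the last two. It widens causality, and only for findings that already pass the newness test.

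**2. Who is exposed to the gap**

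Section 2.3.1 requires PD, with "Hoehn and Yahr Scale stage 1–4", and a SCOPA-night score of at least 7. By eligibility, 17 + 17 = 34 of 34 subjects therefore have at least two pre-existing conditions. Section 2.3.2 lets controlled gastrointestinal, endocrine and cardiovascular disease in as well. This count describes who could be affected. It is not a count of missed events.

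**3. What is recorded by other routes**

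- *SCOPA-S* (night and daytime sleep), Section 2.6.1.1: "The survey will be conducted at baseline (visit 1) and 12 weeks after treatment (visit 4) for both groups".
- *PDSS, ESS, NPI, BDI and PSS*, Section 2.6.3: "scores will be assessed at visits 1–5 for both groups". The Figure 1 caption places these at weeks 0, 4, 8, 12 and 16.
- *Liver, renal and potassium tests*, Section 2.8: baseline, week 4 and week 12.

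Worsening of sleep, sleepiness, neuropsychiatric symptoms, mood and stress therefore leaves a trace in the data, as does laboratory worsening. The visible text names no scale for motor worsening and no measure of comorbidity flares as outcomes. Table 1, which holds the safety schedule, is not shown, so this cannot be confirmed.

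**4. Whether those routes replace adverse-event capture**

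- No visible text sends scale scores to severity grading, causality assessment or the IRB. Section 2.8 sends adverse events there.
- Section 2.9.2 analyses the questionnaires as comparisons between groups. A deterioration of *d* points in one subject moves the mean of an arm of 17 by *d*/17, about 0.06*d* (1/17 = 0.059). A serious individual deterioration can disappear in the mean.
- SCOPA-S has no measurement between weeks 0 and 12. A subject who worsens and leaves before week 12 without that assessment has no post-baseline score. Section 2.9.2 fills missing data by multiple imputation, which supplies an estimate in place of the observed harm.
- Week-16 questionnaire scores are collected, but the questionnaire analysis in Section 2.9.2 names weeks 0, 4, 8 and 12 only.

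The other routes therefore reduce the gap in what is recorded. They do not close the gap in what is handled as an adverse event.

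**The case against.** The strongest case on the other side has five parts.

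- **Worsening is recorded.** A reader might infer from the definition that worsening of existing conditions is never recorded. The documents do not support that. SCOPA-S and five further scales are scored on schedule in both arms, and laboratory tests are repeated. This stands, and the point is confined to capture as an adverse event.
- **Worsening is not expressly excluded.** A reader might also infer that no worsening, however severe, can be an adverse event. The unit is a medical finding, and a first hallucination or a grade never reached before can be read as new. This stands in part: the text is open to a wider reading but does not state it. That leaves the count to the individual investigator.
- **The named product risks are mostly covered.** Section 2.8 names liver and renal damage and hypokalemia. Raised creatinine and transaminases are exclusions, so a later elevation would usually be new, and potassium is tested on the same schedule. This stands. The documents do not name increased sleepiness, gait trouble or neuropsychiatric aggravation as expected harms, and the introduction reports neuropsychiatric benefit for the related formula YKS. The point therefore does not rest on any particular expected harm.
- **Safety oversight does not rest on adverse events alone.** Section 2.8 also relies on laboratory examination, and Section 2.10 gives the committee a general duty to monitor patient safety. This stands. Even so, severity grading, causality review and the report to the IRB are attached to adverse events.
- **The article is a condensation.** The full protocol and the case report form are not shown and may say more. That would answer a complaint about missing detail. Here the article prints a definition, and the printed definition is too narrow.

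**Conclusion.** The point holds in this form: the stated definition is limited to findings that did not occur before the trial and does not count worsening of a pre-existing condition. Aggravation of PD, of sleep disturbance or of a controlled comorbidity may therefore not be captured, graded, assessed for causality or reported to the IRB as an adverse event. The gap looks widest for motor worsening and comorbidity flares.

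The number of events lost cannot be derived from the document. A claim that harm will be undercounted by a given amount, or that the safety conclusion will certainly be falsely reassuring, would go beyond it.

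The conclusion assumes that investigators apply the sentence as printed, and that neither Table 1 nor the full protocol adds worsening to the definition. It is worth correcting before enrolment because the change is small and several safety processes depend on the definition. It affects no sample size, endpoint or efficacy analysis.

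**What to change.** Replace the definition in Section 2.8 with one that covers any undesirable medical finding that is new, or that worsens from baseline in severity or frequency, after the start of the trial and regardless of causality. Keeping the start of the trial as the reference point avoids losing events that occur between entry and the first dose.

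Record each subject's pre-existing conditions with their baseline severity on the case report form, so that worsening can be recognised. Some of this may already exist, since scale scores, laboratory values and Hoehn and Yahr stage are taken at entry. Comorbidities and motor symptoms are the parts to check.

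Reconcile the wider definition with Section 2.5, where the occurrence of adverse events is a criterion for discontinuing the allocated intervention. Widening one passage alone would silently widen the other. The clinical content of that criterion is for the investigators to settle; the two passages only need to be made consistent.

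The cost is one sentence in the protocol, a baseline-conditions entry on the case report form, the reconciliation with Section 2.5 and more events to record.

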### Statistical methods

2.9

#### Sample size

2.9.1

Designed to study the effects of YKSCH in patients with PD experiencing sleep disturbance, this pilot study will use the SCOPA-S score as the primary outcome. A total of 34 subjects (17 in each group) will be needed, based on the effect size demonstrated in a previous study on the effect of doxepin against insomnia in patients with PD,^[9]^ allowing a dropout rate of 10%, a two-sided significance level of 5%, and 80% statistical power.

#### Statistical analysis

2.9.2

Statistical and fNIRS data analyses will be performed by statisticians and a researcher from a different group. An intention-to-treat analysis will be performed in case of subjects lost to follow-up, and multiple imputations will be applied for the missing data. Statistical analysis will be performed using SPSS software for Windows, version 24.0, (Chicago, IL). The SCOPA-S score, which is the primary outcome, will be evaluated by calculating the difference between the mean scores before and after receiving YKSCH or placebo (for treatment or control groups, respectively). Independent two-sample *t*-test (or the Mann–Whitney *U* test for nonparametric samples) will then be performed to analyze the difference between the treatment and control groups. The results of the questionnaire survey, including PDSS, ESS, NPI, BDI, and PSS, scored at 0, 4, 8, and 12 weeks, respectively, and NT levels measured at 0 and 12 weeks will be analyzed using independent two-sample t-tests (or the Mann–Whitney *U* test for non-parametric samples). To compare sleep metrics obtained using PSG and measurement of hormone levels, pre- and post-YKSCH or placebo treatment at weeks 0 and 12, paired t-tests (or the Wilcoxon signed-rank test) will be used. The mean oxyhemoglobin and deoxyhemoglobin concentrations determined using fNIRS at 0 and 12 weeks will be analyzed using repeated-measures analysis of variance. Pearson's correlation coefficient will be used to assess the association among subscales of the questionnaire surveys, oxyhemoglobin and deoxyhemoglobin concentrations, and NT levels. The level of statistical significance will be set at *P < *.05, and 95% confidence intervals will be calculated. A statistician will be consulted incase the obtained data need to be calibrated.

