Here, were report the plans for and design of a study that will evaluate the effects of YKSCH on sleep improvement in patients with PD experiencing sleep disturbance. This study will be a prospective, randomized, double-blinded, placebo-controlled, parallel-group pilot trial. The subjects will be patients with PD who are experiencing sleep disturbances, and these subjects will be randomly assigned to a treatment group or control group at a 1:1 ratio. The intervention will be YKSCH administration in the treatment group and placebo administration in the control group. Subjective and objective assessments of sleep improvement will be performed in this study using a questionnaire survey instrument, polysomnography (PSG), and sleep-related hormone measurements. To elucidate the mechanism underlying the effects of YKSCH in PD, hemodynamic changes in the frontal lobe will be measured using functional near-infrared spectroscopy (fNIRS), and the levels of neurotransmitters (NTs) related to PD will also be evaluated.

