In addition to investigating the mechanism of action of YKSCH on sleep improvement, this study will assess the hemodynamic changes in the frontal lobe during a VFT using fNIRS, and the changes in NT concentrations will also be investigated. In a previous study, prefrontal cortical activation during VFT, assessed using fNIRS, was found to be reduced in chronic insomnia disorder.^[30]^ The purpose of this study is to investigate the mechanism of action of YKSCH in patients with PD exhibiting sleep disorder, by confirming the hemodynamic changes in the frontal lobe caused by the administration of YKSCH.

Sleep disturbance in PD is known to contribute to and exacerbate a variety of other conditions such as mood disorders, primary sleep disorders, night-time motor symptoms, and side effects of PD therapy.^[5]^ There are several studies on the relationship of sleep disturbance with non-motor PD symptoms such as depression, fatigue, and autonomic symptoms,^[5,6]^ and a number of other neuropsychiatric symptoms.^[37]^ Among symptoms associated with sleep disturbance, YKS has recently been mainly reported by several studies as a remedy for behavioral and psychological symptoms of dementia, such as aggressiveness and hallucinations.^[11]^ Therefore, it is expected to be a complementary treatment for sleep disorders related to neuropsychological symptoms, as well as primary sleep disorder, in patients with PD.

This study has some limitations. The study is a small pilot clinical trial. However, this study may be the basis for future large-scaled study because there is no evidence that confirms the effect of YKS of YKSCH on sleep disturbance in PD. In addition, it may be a basis for clarifying the mechanism of action of YKSCH by confirming sleep related hormone changes, identifying hemodynamic changes using fNIRS and neurotransmitter changes after administration of YKSCH. An another limitation, the severity of PD symptoms is not homogenous in all subjects. The interval between taking a dose of conventional and psychologic medication may differ between subjects. However, in an effort to minimize this bias, we are attempting to standardize the interval between taking medication.

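### The primary SCOPA-S comparison is an unadjusted test on change scores; using baseline as a covariate is usually more precise and protects against chance imbalance with 17 per arm

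*Protocol article*

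**What the plan says.** The Sample size section states that "this pilot study will use the SCOPA-S score as the primary outcome". The section on the sleep scale fixes two measurements: "The survey will be conducted at baseline (visit 1) and 12 weeks after treatment (visit 4) for both groups". A baseline score is therefore planned in both arms.

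Under Statistical analysis, the primary outcome "will be evaluated by calculating the difference between the mean scores before and after receiving YKSCH or placebo". An independent two-sample t-test, or a Mann–Whitney test for non-parametric samples, "will then be performed to analyze the difference between the treatment and control groups". No covariate is named for this comparison. The same section plans an intention-to-treat analysis, multiple imputation for missing data and 95% confidence intervals.

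On size: "A total of 34 subjects (17 in each group) will be needed", for 80% power at a two-sided 5% level with 10% dropout. The effect size comes from an earlier doxepin study in PD and is not given as a number. Eligibility includes "SCOPA -night score ≧7; Hoehn and Yahr Scale stage 1–4".

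**The concern.** The planned comparison assumes that a patient who starts one point higher also ends one point higher. For a questionnaire measured with error, the regression of week-12 score on baseline normally has a slope below 1. Where it does, the change score subtracts too much of the baseline. This has two consequences.

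- **Precision.** The baseline noise that is subtracted in excess stays in the change score and widens its standard error.
- **Chance imbalance.** If one arm happens to start worse, regression to the mean makes it appear to improve more, whatever the drug does. With 17 per arm such imbalances are common, and the article names no stratification of the randomisation by baseline score.

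The article calls the trial a pilot, but it sizes it by a power calculation for this outcome, so precision matters by its own standard. ANCOVA uses the same two measurements and estimates the slope from the data.

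**Working it through.** **Inputs from the protocol article.** 17 per arm, "randomly assigned to a treatment group or control group at a 1:1 ratio", two-sided 5%, 80% power, 10% dropout. **Not given, so assumed:** effect size, SDs, and the correlation r between baseline and week-12 SCOPA-S.

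**1. What the stated sample size implies.** It cannot be reproduced forwards without an effect size. Working back, 15/0.9 = 16.7, which rounds up to 17, so the plan fits 15 evaluable per arm. The standardised difference detectable with 80% power is then √(2/15) × (1.960 + 0.842) = 1.02 by the normal approximation, or d = 1.06 by the noncentral t. I take d = 1.06 to be on the change-score scale, so that the planned t-test has exactly its stated power.

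**2. Variance ratio.** Let σ be the week-12 SD and kσ the baseline SD.

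- Var(change) = σ²(1 + k² − 2kr) = σ²[(1 − r²) + (k − r)²]
- Var(ANCOVA) = σ²(1 − r²)
- Ratio = (1 − r²) / [(1 − r²) + (k − r)²]

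With equal SDs (k = 1) this reduces to (1 + r)/2. It is below 1 unless r = k, that is, unless the true slope r/k equals 1.

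**3. Power.** The ANCOVA effect size is 1.06/√ratio. It is divided by √(1 + 1/26) as the small-sample penalty for estimating the slope (2n − 4 = 26 at n = 15) and tested on 2n − 3 = 27 degrees of freedom. The planned test has 80% in every row.

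| k (baseline SD / week-12 SD) | r | Variance ratio | ANCOVA power |
|---|---|---|---|
| 1.0 | 0.3 | 0.65 | 93% |
| 1.0 | 0.5 | 0.75 | 89% |
| 1.0 | 0.7 | 0.85 | 85% |
| 1.0 | 0.8 | 0.90 | 82% |
| 0.8 | 0.3 | 0.78 | 87% |
| 0.8 | 0.5 | 0.89 | 83% |
| 0.8 | 0.7 | 0.98 | 79% |
| 0.7 | 0.3 | 0.85 | 85% |
| 0.7 | 0.5 | 0.95 | 80% |
| 0.7 | 0.7 | 1.00 | 78% |

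The worst case is a loss of about 2 percentage points, when the slope is exactly 1 and only the penalty remains.

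**4. If d = 1.06 is instead on the raw-score SD scale** (equal SDs), change-score against ANCOVA power is 66% against 82% at r = 0.3, 80% against 89% at r = 0.5, and 95% against 97% at r = 0.7. Below r = 0.5 the change score is noisier than the week-12 score alone: 2(1 − 0.3) = 1.4 times its variance at r = 0.3.

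**5. Chance imbalance.** With 17 per arm, the standardised baseline difference has SD √(2/17) = 0.34. A gap above 0.3 SD arises in about 38% of randomisations and above 0.5 SD in about 14%. With equal SDs, a gap of g shifts the expected change-score difference by (1 − r)g. For g = 0.5 SD and r = 0.5 this is 0.5 × 0.5 = 0.25 SD in favour of the arm that started worse. ANCOVA removes this shift.

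**The case against.** The strongest reply is that nothing here is an error. Under randomisation a two-sample test on change is unbiased over repeated allocations and keeps its type I error, the trial is described as a pilot, and the gain from ANCOVA depends on quantities that the article does not give. All of that stands, except that pilot status does not make power irrelevant once the sample size rests on it.

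It is also fair to object to equal SDs. An entry cut-off tends to compress the baseline spread more than the week-12 spread, which moves k below 1 and shrinks the gain. That is why the table includes k = 0.8 and 0.7.

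Some stronger readings are tempting, and the text does not support them:

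- **That the baseline is ignored.** It is subtracted. It is only not used as a covariate.
- **That the entry cut-off biases the comparison.** The cut-off is on the night score, while the primary outcome covers night and day. Regression to the mean from a cut-off affects both arms alike. The between-arm distortion comes from chance imbalance combined with a slope below 1.
- **That the Discussion concedes baseline imbalance.** Its remark that "the severity of PD symptoms is not homogenous in all subjects" concerns disease severity, not SCOPA-S at baseline.
- **That the Mann–Whitney option breaks a promised confidence interval for the mean difference.** The article promises 95% intervals without naming the quantity, and a Hodges–Lehmann shift with an interval can accompany the rank test. The rule for choosing between the tests and the mechanics of pooling imputations may properly sit in an analysis plan that is not shown.

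**Conclusion.** The point holds as a matter of efficiency and robustness, not validity. The article fixes an unadjusted change-score test as primary although ANCOVA could be run on the same data.

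With equal SDs and d = 1.06 on change, the planned 80% power would become about 82% to 93% for r from 0.8 down to 0.3. With a baseline SD of 0.7 to 0.8 of the week-12 SD, and r from 0.3 to 0.7, it would be about 78% to 87%. The gain therefore runs from material to nil, and the downside is about 2 percentage points at worst. Protection against chance imbalance comes in addition wherever the slope differs from 1.

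A reader might turn the equal-SD ratios into sample sizes: 34/0.65 = 52, 34/0.75 = 45 and 34/0.85 = 40 patients on change scores to match ANCOVA in 34. Those figures are the favourable end of the range. They assume equal SDs, omit the penalty for estimating the slope, and should not be quoted as the expected gain.

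**What to change.** In the Statistical analysis section, make the primary analysis a single pre-specified ANCOVA of week-12 SCOPA-S score, with arm and baseline SCOPA-S score as terms, in all randomised subjects. Pool the estimates over the planned imputations and report the adjusted mean difference with its 95% confidence interval. Keep the change-score t-test, or a rank-based test, as a sensitivity analysis rather than as an alternative primary test.

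The cost is about one sentence of text and one degree of freedom. No extra visit, measurement or patient is needed.

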**Figure 1 F1:**
[figure not shown]
Schedule of YKSCH or placebo treatment and collection of outcome measurements. The treatment or control groups will be administered YKSCH or placebo drug, respectively. The subjects will receive YKSCH or placebo for 12 weeks, and be followed-up for 4 weeks. Administration of SCOPA-S, to assess primary outcome; PSG; collection of blood samples for analysis of NT and hormone levels; fNIRS measurement will be performed at 0 and 12 weeks (indicated by black arrows). Questionnaire surveys related to sleep disturbance will be conducted at 0, 4, 8, 12, and 16 weeks (indicated by black and hollow arrows). fNIRS = functional near-infrared spectroscopy, NT = neurotransmitter, PSG = polysomnography, SCOPA-S = Scales for Outcomes in PD-Sleep Scale, YKSCH = Yokukansankachimpihange.

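### Five secondary questionnaires are collected to week 16, but their stated analysis stops at week 12 and uses two-sample t-tests with no main time point and no baseline adjustment

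*Protocol article*

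**What the plan says.** All places are in the Protocol article.

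- **Collection.** The Figure 1 caption states: "Questionnaire surveys related to sleep disturbance will be conducted at 0, 4, 8, 12, and 16 weeks". Section 2.6.3 says of PDSS, ESS, NPI, BDI and PSS that "scores will be assessed at visits 1–5 for both groups".
- **Timeline.** Section 2.7: "The total study duration will be 16 weeks, including a 12-week treatment period and a 4-week follow-up period".
- **Analysis.** Section 2.9.2 states that "The results of the questionnaire survey, including PDSS, ESS, NPI, BDI, and PSS, scored at 0, 4, 8, and 12 weeks, respectively", together with the neurotransmitter levels, "will be analyzed using independent two-sample t-tests", with Mann–Whitney as the alternative. One threshold serves all analyses: "The level of statistical significance will be set at" P < .05. 95% confidence intervals are promised, and missing data are to be handled by multiple imputation under intention to treat.
- **Contrast within the section.** A before/after difference is defined for SCOPA-S only. Repeated-measures ANOVA is assigned to fNIRS only.

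**The concern.** There are two problems, both visible in the text itself.

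First, the list of weeks to be analysed differs from the list of weeks collected, and the missing one is the only off-treatment visit. If the section is followed as written, the trial has no planned efficacy result on whether any benefit persists or reverses after treatment stops.

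Second, measures repeated in the same patients are given a two-sample test with no named week and no baseline covariate. Each instrument then yields several P values and no single answer. Read literally, one comparison falls at week 0, where any difference between randomised arms is due to chance. The article intends the results as a basis for further studies, so a chance finding among the secondary outcomes could steer that work.

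**Working it through.** **Step 1. Which efficacy measures fall in the follow-up.**

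| Measure | Collected (weeks) | Weeks named in 2.9.2 |
|---|---|---|
| SCOPA-S | 0, 12 | before/after |
| PSG, hormones | 0, 12 | 0, 12 |
| Neurotransmitters | 0, 12 | 0, 12 |
| fNIRS | 0, 12 | 0, 12 |
| PDSS, ESS, NPI, BDI, PSS | 0, 4, 8, 12, 16 | 0, 4, 8, 12 |

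Safety laboratory tests are at baseline, week 4 and week 12 (section 2.8). In the text, week 16 therefore holds the five questionnaires and no other efficacy measure, and the questionnaires are the only row where the two columns disagree. Table 1 is not shown, so this rests on the text and the Figure 1 caption.

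**Step 2. Number of tests.** Five instruments cannot pair one-to-one with four weeks, so the list must mean that each instrument is scored at each listed week. Post-baseline tests: 5 × 3 = 15. This count is the same for raw scores and for change from baseline.

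**Step 3. False positives with no true effect, independent tests.** Expected number: 15 × 0.05 = 0.75. Chance of at least one: 1 − 0.95^15 = 0.537.

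**Step 4. The same with correlated tests.** The document gives no correlations, so these are assumptions. The sample size section gives 17 per arm, "allowing a dropout rate of 10%, a two-sided significance level of 5%, and 80% statistical power". 17 × 0.9 = 15.3, so 15 per arm were simulated. Scores were normal with equal correlations, 20,000 trials per setting (Monte Carlo standard error below 0.4 percentage points).

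| Correlation between instruments | Correlation over time | Raw scores | Changes |
|---|---|---|---|
| 0.3 | 0.5 | 46% | 46% |
| 0.3 | 0.8 | 37% | 46% |
| 0.5 | 0.5 | 42% | 42% |
| 0.5 | 0.8 | 34% | 41% |
| 0.7 | 0.5 | 34% | 34% |
| 0.7 | 0.8 | 28% | 36% |

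A separate raw-score run at (over time, between instruments) = (0.6, 0.3), (0.7, 0.4) and (0.8, 0.5) gave 45%, 40% and 33%. For between-instrument correlations of 0.3–0.5 the range is thus about 33–46%. It falls to 28% only for raw scores at the strongest pair tried.

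**Step 5. One named week.** Five week-12 contrasts: 1 − 0.95^5 = 0.226 if independent, and 15–21% in the simulation for between-instrument correlations of 0.3–0.7. Holm adjustment over the five would hold it at 5% or less.

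**Step 6. Why raw score or change matters.** With equal variances and baseline–visit correlation ρ, the variance of the arm difference, relative to raw scores, is 2(1 − ρ) for change and about 1 − ρ² with baseline as a covariate.

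- ρ = 0.5: change 2 × 0.5 = 1.00; adjusted 1 − 0.25 = 0.75.
- ρ = 0.8: change 2 × 0.2 = 0.40; adjusted 1 − 0.64 = 0.36.

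The unstated choice can alter precision considerably, and baseline adjustment is the most precise of the three at either value.

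**The case against.** The best defence is that these are secondary outcomes in a self-described pilot with one primary instrument. No success rule depends on them, and a condensed article may leave visit hierarchy and multiplicity to an analysis plan. Confidence intervals and multiple imputation are already planned, which covers part of any remedy. This stands as a limit on severity, and it is why multiplicity adjustment is only optional here. It does not remove the point: the article names the weeks and the test, and the weeks disagree with its own schedule.

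A reader might infer more than the text supports:

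- **Twenty tests, five of them at baseline.** 5 × 4 = 20 is one literal reading. The section never says that each week is tested separately, and the preceding SCOPA-S sentence compares before/after differences, so a change-score reading with 15 tests and no baseline test is equally open. Baseline comparisons also carry no efficacy claim and do not belong in an error rate for efficacy.
- **Invalid tests because repeated values are correlated.** A between-arm test at one visit, or on one change score, uses one value per patient, so correlation over time does not distort its type I error. The loss is precision and a single summary.
- **Follow-up that exists only for these questionnaires, or week-16 data that are excluded.** No purpose of the follow-up is stated, adverse events may be recorded then, and the section omits week 16 without ruling it out.

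**Conclusion.** The point holds for the secondary questionnaires. The week-16 mismatch between collection and analysis is certain from the text and does not depend on how the t-tests are read. The stated test also leaves each instrument without a main time point, a baseline adjustment or a defined quantity to compare (raw score or change).

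The size is about 15 post-baseline tests. The chance of at least one false positive is 54% under independence and roughly 33–46% under plausible but assumed correlations, somewhat lower if the instruments overlap very strongly. The primary SCOPA-S comparison and its 5% level are untouched. This should be corrected before unblinding, but it does not threaten the trial's main result.

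**What to change.** For each of PDSS, ESS, NPI, BDI and PSS, replace the t-tests with one longitudinal model on weeks 4, 8, 12 and 16, containing arm, visit, arm-by-visit and baseline score and allowing for correlation within patient. Name the week-12 arm difference as the main result for that instrument and the week-16 difference as the off-treatment contrast. Do not test week 0; describe baseline by arm instead. Report estimates with 95% confidence intervals and label them exploratory. Holm adjustment over the five week-12 contrasts is optional.

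Merely adding week 16 to the present list would not be enough: it would raise the post-baseline tests from 15 to 5 × 4 = 20 and still give no single result per instrument.

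The cost is a rewording of section 2.9.2, modest extra analysis and fewer nominally significant secondary results. No patients, visits or measurements are added.
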